### N-of-1 Clinical Trial

To zoom in on specific treatment effects, 4 single case studies with an A^1^B^1^A^2^B^2^design (single time series) will be conducted, of which 2 single case studies will apply an actual SMR-neurofeedback protocol and 2 single case studies will apply a sham neurofeedback training. The clinical trial will be single-blinded, indicating that participants do not know which part of the training they will receive. Participants are selected from the control group of the previously described RCT protocol who have already completed pre- (T0) and posttreatment (T1) measurements. Inclusion in the n-of-1 trial will be selective: participants with the highest scores on outcome measures on T1 of the RCT will be approached first as it is believed that these patients have the highest need for treatment. However, allocation to treatment (sham or real) will be random.

For a detailed description of this design of n-of-1 studies, see Rizvi and Nock [42]. Basically, in this design, a baseline period (A^1^: no treatment, lasting 3 weeks) is followed by a treatment period (B^1^: neurofeedback, sham or real, lasting 4 weeks and resulting in 8 neurofeedback sessions), which is followed by a period where treatment is withdrawn (A^2^: lasting 3 weeks). During all periods, outcome measures DAQ-SF and BIS-11 will be assessed 2 times per week. At the end of the A^2^period, statistical analyses are applied to test for significant improvements in study end points. In cases of significant improvement during treatment, a second period of neurofeedback, B^2^(sham or real), will be applied. This way, if neurofeedback does not prove to be effective within B^1^, participants will not be burdened with the requirement of completing more sessions. It is expected that patients who have not shown any significant improvement during neurofeedback sessions in B^1^will not show any further improvements when undergoing more sessions. After completion of the study, patients and treatment supervisors will be debriefed about whether the neurofeedback intervention was real or sham.

To test for transient effects of the neurofeedback intervention, a follow-up measurement of resting state EEG, BIS-11, DAQ-SF, and cued go/no-go task will be performed 12 months after completing the posttreatment measures for both participants in the intervention group of the RCT and for participants in the n-of-1 clinical trial.

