**Methods:**

Participants will be male SUD patients with various comorbidities residing in an inpatient forensic treatment facility approached through treatment supervisors for participation. Participants have tested positive for drug use in the past 24 months. The study consists of 2 parts: a randomized controlled trial (RCT) and a n-of-1 clinical series. In the RCT, 50 patients will be randomly assigned to an intervention (n=25) or a control (n=25) condition. Patients in the intervention group will receive 20 SMR neurofeedback sessions aimed at reducing impulsivity; participants in the control group receive treatment-as-usual (TAU). Additionally, 4 in depth n-of-1 clinical trials will be conducted where effects of an SMR neurofeedback intervention will be compared to effects of sham neurofeedback.

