Several studies have shown neurofeedback to be a promising intervention for various disorders, ranging from SUD to attention deficit hyperactivity disorder (ADHD) [16]. In SUD, a widely used neurofeedback protocol is the Scott-Kaiser modification of the Peniston Protocol, consisting of a combination of sensorimotor rhythm feedback (SMR, 12-15 Hz) followed by alpha-theta based feedback [17]. With this type of protocol, patients first receive neurofeedback that focuses on reinforcing SMR (12-15 Hz) while inhibiting slower frequencies such as delta (2-5 Hz) and theta (5-8 Hz) and also inhibiting high beta (ranging from 18-30 Hz) [15,17]. This type of feedback is first employed for 10 to 20 sessions before the neurofeedback protocol is switched to an alpha-theta based protocol, where alpha (ranging from 8-12 Hz) is decreased while theta (5-8 Hz) is augmented until the amplitude of alpha drops below the level of theta [15,17]. The Scott-Kaiser modification of the Peniston Protocol has shown to be effective in opiate-dependent patients as well as in patients with a mixed substance dependency, as it led to the reduction of feelings of craving [15], a powerful predictor of relapse in drug-taking [20-21] and therefore promoted treatment attendance and abstinence rates of participants [17]. As most criminal offenders with SUD also suffer from comorbid psychiatric conditions however, treatment with neurofeedback may become more complicated [16]. For patients having a combination of impulsivity issues due to comorbidity with other psychiatric disorders, as well as substance abuse problems, it is suggested that an SMR-enhancing neurofeedback protocol should be applied to address the issue of impulsivity first [22]. Studies performing a neurofeedback protocol consisting of suppressing slow waves such as theta (4-7 Hz) and enhancing faster waves such as SMR (12-15 Hz) have demonstrated an improvement of impulse control in a population of students (in Egner and Gruzelier [23], for example) and have shown to positively affect motor control and cortical inhibitory function (in Sokhadze et al [16], for example). This type of neurofeedback protocol is also commonly applied with patients suffering from the hyperactive-impulsive ADHD subtype, and there are many studies reporting reduction in impulsivity after treatment (in Fuchs et al [24], for example). Several studies have shown that impulsivity and craving for substances are strongly correlated no matter the administered drug of choice. For example, in a study by Tziortzis et al [25] with methamphetamine users, individuals with higher levels of impulsivity reported significantly more craving than individuals scoring lower on impulsivity. In alcohol-dependent patients, higher scores of craving were correlated with higher self-reported impulsivity on the BIS-11 [26]. Moeller et al [27] found a significant correlation between the motor impulsivity subscale of the BIS-11 and craving in a population of cocaine-dependent subjects. Also for cocaine-dependent patients, higher impulsivity was associated with greater severity of addiction symptoms such as craving [28,29]. Also, contemporary neuropsychological models stress impulsivity and SUD to be the result of the same imbalance between bottom-up and top-down neural systems [30,31]. Bottom-up systems concern subcortical brain circuitry promoting impulsive reward behavior (regardless of long-term outcomes), whereas top-down processes concern reflective and self-control functions driven by prefrontal brain circuitry [32]. Within SUD, chronic substance abuse may produce neural changes leading to a structural state of disinhibition and impulsivity [33,34], causing immediate reaction to substance-related cues that elicit craving [35]. Not only acute but also prolonged effects of substance abuse have proven to be of great influence in disrupting these neuropsychological mechanisms, therefore maintaining problems with inhibitory control even after drug use is terminated [36]. Although impulsivity and craving are both independently identified as key elements in SUD, to date, there has been no study investigating whether a reduction in one will also lead to a reduction of the other.

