### Intervention

All participants already receive TAU at the moment of inclusion. They will continue to do so during the course of this trial. Type of TAU is dependent on disorder and behavior but can range from cognitive behavioral therapy, psychotherapy, and psychomotor therapy to relapse prevention treatment and can be either individual treatment or in-group treatment. Treatment can also be supplemented by medication for psychotic symptoms or depressive symptoms, for example. In some rare cases, aversion or craving reducing medication is prescribed.

Participants in the intervention condition of the RCT will receive 20 neurofeedback sessions, each lasting approximately 40 minutes. EEG magnitude is measured across delta (0.5-3.5 Hz), theta (3.5-7.5 Hz), alpha (7.5-12 Hz), beta (12-20 Hz), SMR (12-15 Hz), high beta (20-32 Hz), and gamma (32-49 Hz) frequency bands. To reduce inattention and impulsivity, a conventional neurofeedback protocol will be used that consists of suppressing theta magnitude and enhancing SMR magnitude [49,50]. The aims of the neurofeedback sessions are therefore to reduce slow waves (specifically theta, 3.5-7.5 Hz, and if necessary delta, 0.5-3.5 Hz) and increase faster waves (SMR, 12-15 Hz). A maximum of 3 different frequency bands will be trained during each session. Neurofeedback training will be performed on the EEG signal recorded from electrode position Cz against a right ear mastoid reference.

For the n-of-1 design of the trial, 2 participants will receive the SMR-neurofeedback intervention and 2 participants will receive sham neurofeedback.

Real and sham neurofeedback procedures will be similar (eg, electrode position, preparation, instructions given to participants) except that for the sham neurofeedback training group, participants are instructed to enhance an irrelevant frequency band that is randomly chosen from higher beta bands (20-23 Hz, 23-26 Hz, 26-29 Hz, and 29-32 Hz). Therefore, no specific frequency band is systematically modulated and thus should not result in desired treatment outcomes. Participants will still be given positive feedback and be able to influence the video games in order to minimize possible irritation of participants.

Neurofeedback will be applied as implemented within the BrainMarker software engine (BrainMarker Device, Brainmarker BV Gulpen).

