## Discussion

This study aims to evaluate the efficacy of an SMR-based neurofeedback treatment on reducing impulsivity in a population of inpatient forensic patients. Possible effects of a reduction in impulsivity on substance abuse will be assessed as well. We expect a significant reduction in impulsive behavior, level of craving, and actual drug use for participants receiving the SMR-neurofeedback protocol. The n-of-1 approach might help to explain effects possibly found in the RCT study since it allows for a more direct focus on treatment effects by following participants closely and thereby being able to directly attribute behavioral and neurophysiological change to the SMR-neurofeedback protocol employed. The study aims to extend previous findings on the efficacy of neurofeedback treatment in reducing impulsivity, not only by linking possible findings regarding a reduction of impulsivity to substance abuse symptoms but also by examining effects in a forensic psychiatric population with various comorbid disorders.

Studies about the efficacy of neurofeedback in a psychiatric forensic setting, in which the population is characterized by various comorbidities and various kinds of medication, are lacking. In our study, exclusion criteria are kept to a minimum to include as many participants with SUD as possible and to be able to generalize effects of an SMR-neurofeedback treatment over different types of comorbidities.

Although RCTs with a treatment and a sham treatment arm are considered the gold standard in research, conducting large trials is often times difficult in forensic settings; treatment motivation might be low for the type of patients in the treatment facility because they are placed under compulsory inpatient custody and are not seeking treatment due to inner motivation for change. In RCTs, number of participants usually has to be quite high to reach the desired effect size [54]. Participating patients might be even less inclined to take part in the trial if they know that they might end up in a placebo condition.

By employing an n-of-1 approach combined with an RCT, this study might help shed light on the underlying mechanisms of neurofeedback because an n-of-1 approach allows closer monitoring of treatment effects and provides valuable insight into an individual’s treatment progress that might otherwise be lost in a between-group design [42].

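### Each n-of-1 patient receives only real or only sham neurofeedback, so the series cannot by itself attribute change to SMR training as the article says it can

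*Protocol article*

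**What the plan says.** **Allocation.** The N-of-1 Clinical Trial section describes four A1-B1-A2-B2 cases, of which "2 single case studies will apply an actual SMR-neurofeedback protocol and 2 single case studies will apply a sham neurofeedback training". The Intervention section repeats the split at the level of the person: "2 participants will receive the SMR-neurofeedback intervention and 2 participants will receive sham neurofeedback". The section also says that "allocation to treatment (sham or real) will be random", that participants are blinded, and that afterwards patients and treatment supervisors are told which type was given.

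**Phases.** A1 is three weeks without treatment, B1 is four weeks with eight sessions of the assigned type, and A2 is a three-week withdrawal. The DAQ-SF and BIS-11 are completed twice a week. B2 is conditional: "In cases of significant improvement during treatment, a second period of neurofeedback" is given; otherwise the case ends after A2.

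**Purpose and claims.** This Study (Introduction) explains that the RCT has no sham arm, that knowledge of sham effects is needed to tell specific from nonspecific effects apart, and that the n-of-1 trials are added to cope with the RCT's limitations. It expects changes to be attributable to neurofeedback with more certainty. The Abstract (Methods) describes the series as one "where effects of an SMR neurofeedback intervention will be compared to effects of sham neurofeedback". The Discussion speaks of "being able to directly attribute behavioral and neurophysiological change to the SMR-neurofeedback protocol employed", and the Abstract (Conclusions) makes the same claim.

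**Analysis.** The N-of-1 Trial part of Statistical Analysis plans, within each case, inspection of autocorrelation followed by tests of level, slope and trend. It names no real-versus-sham contrast.

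**The concern.** The strength of a single-case design is that each patient is his own control. That strength applies only to conditions that the same patient experiences. Here the conditions within a man are his assigned training and nothing at all. The contrast that the article needs, SMR training against an otherwise similar procedure without SMR training, does not occur within any man.

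This matters because the n-of-1 series is the trial's only source of sham evidence. The RCT compares neurofeedback plus usual treatment with usual treatment alone, so it cannot separate SMR from the rest of the package. If the series is then reported as having made that separation, readers will credit the trial with a mechanistic conclusion that neither part can deliver.

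**Working it through.** **1. What each man's own series compares**

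| Cases | A1 | B1 | A2 | B2 (only after improvement) | Contrast within the man |
|---|---|---|---|---|---|
| 2 | none | real | none | real | real vs nothing |
| 2 | none | sham | none | sham | sham vs nothing |

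Ratings before B2, at two per week: 3×2 = 6 in A1, 4×2 = 8 in B1 and 3×2 = 6 in A2, so about 20 per man and outcome. All of them bear on the contrast in the last column.

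**2. What the change contains.** Write S for the SMR-specific effect, N for the average nonspecific effect (trainer contact, expectancy, attention) and P for the man's own departure from that average.

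- Change in a man on real training: S + N + P(man)
- Change in a man on sham: N + P(man)

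No number of ratings within a man on real training separates S from N. The difference of group means is S + [mean P of two men − mean P of two other men].

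**3. How precise that difference is.** If individual changes vary between men with standard deviation σ, the standard error of a 2-versus-2 difference is σ × √(1/2 + 1/2) = σ, one whole between-person standard deviation. More ratings per man reduce measurement noise but not variation between men.

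**4. Randomisation reference.** Number of ways to choose 2 of 4 men: 4!/(2!·2!) = 6. Smallest attainable p: 1/6 = 0.17 one-sided, 2/6 = 0.33 two-sided. This holds whatever the data.

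**5. Parametric reference.** The article gives no sample size or power for the n-of-1 part, so there is no figure of its own to reproduce there. Its RCT figure of 21 per condition does reproduce from an exact two-sample t-test, one-sided 0.05, with a standardised mean difference of 0.80 (power 0.817). Carrying that same 0.80 to 2 versus 2 gives 2 degrees of freedom and noncentrality 0.80 × √(2/2) = 0.80. Power is 0.14 one-sided and 0.08 two-sided. For 80% power the difference would have to be about 4.0 standard deviations one-sided, or 5.7 two-sided.

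**6. Replication.** B2 repeats the same type and is run only in men judged improved. It can show whether an improvement recurs in a man selected for having improved. It adds no real-versus-sham information within a man, and it is missing for the men in whom B1 did nothing.

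**The case against.** **The design does offer something.** Types are allocated at random, participants are blinded, treatment is withdrawn, and band magnitudes are computed for each session. Four such courses are useful illustrations, and the article partly hedges by saying that the series might help to explain the RCT. This stands, and it is why the right description is a descriptive one. Random allocation prevents systematic selection into real or sham; with two men per type it does little against chance differences between them. The blinding described covers participants only.

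**The 1/6 floor concerns a test nobody planned.** This is correct. The planned tests are within cases. A reader might infer that the planned analysis is bound to fail; the article does not support that. The figure only shows how much the real-versus-sham comparison announced in the Abstract could carry.

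**One type per man is a defensible choice.** Neurofeedback is presented as operant learning, so a man given real training first may carry the skill into a sham period, and a change of feedback could unblind him. This stands. A reader might infer that the trial must switch to real and sham within each man. That does not follow: randomising order once in each of four men would itself reach only 1/2⁴ = 1/16 = 0.06, and running both periods in everyone would remove the plan's condition for B2.

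**Might a man receive both types?** The mention of sham or real again at B2, and of participants not knowing which part of the training they get, could be read that way. The split by participant in the Intervention section and the debriefing on a single type point the other way.

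**Is the sham contradicted elsewhere?** A reader might infer this because sham "participants are instructed to enhance an irrelevant frequency band that is randomly chosen from higher beta bands", while the Introduction describes a protocol that inhibits high beta. That passage describes a different published protocol. This trial suppresses theta (and delta if necessary) and enhances SMR, so the two passages do not conflict.

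**Can the chance rate of reaching B2 be stated?** A reader might want to attach a rate. The article does not fix the test closely enough: it follows a cited method after inspection of autocorrelation, is applied at the end of A2, and counts improvement only. No rate is claimed here.

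**Conclusion.** The claim as worded exceeds what the allocation can support. Within a man, the series can show that scores moved when his assigned training started or stopped. It cannot show that SMR training, rather than the nonspecific parts of the procedure, moved them. The only comparison that bears on that question is two men against two, with a standard error of one between-person standard deviation and a smallest one-sided randomisation p of 1/6 = 0.17.

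This rests on reading the plan as one type per man, on untreated A phases, and on real variation between men in how they respond. The article supports the last by describing its inclusion criteria as lenient and its sample as likely heterogeneous. The power figures also assume normal errors and borrow the RCT's 0.80.

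The point is limited to the n-of-1 conclusions. The RCT comparison of neurofeedback plus usual treatment with usual treatment alone is unaffected, and the n-of-1 series keeps its value as description.

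**What to change.** Reword the n-of-1 statements in the Abstract (Methods and Conclusions), in This Study and in the Discussion. Suitable text would be:

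> The n-of-1 series describes the individual course of each patient under real or sham neurofeedback compared with no treatment. Real and sham are compared descriptively, between persons. With two patients per type, the series cannot by itself attribute change to SMR training. A second training period is available only for patients selected on significant improvement after the first, and its results are reported as such.

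The cost is a more modest stated conclusion. Patients, phases, measurements and the condition for B2 all stay as they are.

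If the sponsor wants to keep an attribution claim, a randomised and masked real/sham comparison within each patient is an option to weigh. It would bring possible carry-over and unblinding, would conflict with the present condition for B2, and would need several randomised blocks per patient to test at 0.05. It is not required by this point.

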### Participants

A power analysis calculation for the RCT using G*Power 3 (Department of Psychology) based on a 1-tailed alpha value of .05, a power value of 0.80, and an effect size (*f*) of 0.80 yielded a recommended sample size of 21 participants each in the control and intervention conditions. Given the special research population we aim to select 25 participants for each condition.

Participants are male patients diagnosed with SUD (substance dependency or substance abuse) according to the *Diagnostic and Statistical Manual of Mental Disorders*, Fourth Edition, Text Review (DSM-IV-TR [43]) and currently staying at the treatment facility. Participants have tested positive for drug use in the past 24 months at time of inclusion. Drug use is operationalized as urine, saliva, or breathalyzer analysis testing positive for either marijuana and/or psychostimulant/opioid drugs and/or alcohol. Corresponding with treatment facility policy, nonprescribed medication that is used for recreational drug consumption such as inhaled methylphenidate will also be scored as positive drug testing, as will refusal to undergo drug testing.

Participants are allowed to continue using prescription medication (as prescribed by a psychiatrist or general physician of the treatment facility) but are required to inform researchers of any medication they are currently using or any change in medication during treatment with neurofeedback.

### Recruitment

Recruitment will start with the selection of patients for the RCT part of the study. Participants are approached through treatment supervisors for participation. Treatment supervisors are informed about the general inclusion criteria for this study. Out of all participants that meet the requirements, a random sample of 50 will be drawn and randomly assigned to 1 of the 2 conditions (intervention and control). Prior to participation in the trial all participants are asked to provide written consent. If at this point a participant chooses not to participate in the trial, this will be coded as a nonresponse. Missing numbers of participants will be complemented by randomized allocation of other suitable participants who are willing to participate in order to guarantee the sample size. Once all patients for the RCT have been recruited, recruitment for the n-of-1 clinical trial will begin. All participants will receive a financial reward after completing pre- and posttreatment measurements.

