The study will combine a randomized controlled trial (RCT) design with an n-of-1 clinical trial. The RCT allows for investigating to what extent an SMR-neurofeedback protocol can reduce craving and actual drug use by augmenting levels of impulsivity for forensic psychiatric patients at a group level. However, RCTs have several disadvantages. First, they focus on between-group differences, making it difficult to determine the exact working mechanisms of neurofeedback at the single patient level. Despite the fact that the number of studies employing neurofeedback has increased over the past 2 decades, to date the underlying working mechanisms of neurofeedback remain unclear. Success of treatment is usually determined by a reduction in subjective complaints or based on other behavioral measures, independent of patients’ responses to neurofeedback on a neurophysiological level (eg, change in mean amplitude of brain frequencies). Second, most RCTs focus on participants with single, well-defined disorders or diagnoses, making it difficult to apply previous findings to patients who have a more complex psychopathology as is usually the case in forensic patients. Third, finding a reduction in subjective complaints could partially be explained by the interaction with the person giving the treatment, as this occurs with almost all frequently given types of therapy in the psychological field [37]. To rule this out, large RCTs with a treatment and a sham arm are necessary. Unfortunately, these studies are very difficult to conduct in a forensic psychiatric setting due to the fact that forensic patients generally have low levels of treatment compliance [38]. As the current study concerns a single-site study with only a limited number of patients who fit the inclusion criteria to begin with (but on forehand sufficient according to power analysis), adding a sham arm to the RCT would most likely further reduce the motivation of patients to participate and hence increase nonresponse. However, insight into possible sham effects is needed to differentiate between specific and nonspecific treatment effects which are independent of the neurofeedback trainer. Finally, RCT studies showing treatment effects of neurofeedback often vary in the applied protocols, number of sessions, and treatment intensity. To date, there have been no guidelines developed that specify these neurofeedback parameters. Especially for forensic patients, developing a treatment that is well applicable and helps to reduce symptoms of SUD is of great importance, as forensic treatment is aimed at protecting society and reducing the risk of reoffending. By adding several n-of-1 clinical trials we attempt to cope with these disadvantages. A well-conducted n-of-1 trial allows testing of the specific working mechanisms of neurofeedback in a single patient and is therefore able to detect detailed behavioral and neurophysiological changes that can then be attributed more definitely to neurofeedback treatment.

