### Randomized Controlled Trial

A randomized controlled trial with N=50, where 25 participants are randomly assigned to treatment as usual (TAU) combined with 20 SMR-based neurofeedback sessions and 25 participants are randomly assigned to TAU only, without neurofeedback intervention. The 2 groups are compared pretreatment (T0) and posttreatment (T1) on variables linked to the research questions. Both groups will receive pre- and posttreatment measurements with an interval between T0 and T1 of approximately 10 weeks in which participants in the intervention group will receive 20 neurofeedback treatment sessions and participants in the control condition will follow TAU.

The design of this part of the study is a 2×2 design with the condition (neurofeedback vs TAU) as a between-subjects factor and time as a within-subjects factor (pre- and postintervention).

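### The recruitment section allocates patients before asking for consent and replaces those who decline, so refusal can depend on the arm and the groups analysed may not be the groups randomised

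*Protocol article*

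**What the plan says.** The Recruitment section gives the steps in this order:

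1. Eligible patients are reached through treatment supervisors, and from them "a random sample of 50 will be drawn and randomly assigned to 1 of the 2 conditions".
2. "Prior to participation in the trial all participants are asked to provide written consent".
3. "If at this point a participant chooses not to participate in the trial, this will be coded as a nonresponse".
4. "Missing numbers of participants will be complemented by randomized allocation of other suitable participants who are willing to participate", so that the sample size is kept.

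The two conditions differ visibly. Under Randomized Controlled Trial, "25 participants are randomly assigned to TAU only, without neurofeedback intervention". Under Intervention, the other arm "will receive 20 neurofeedback sessions, each lasting approximately 40 minutes", on top of the same usual treatment. The financial reward is described once, for all participants, and is tied to completing the measurements before and after treatment.

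The authors expect willingness to be a problem. Under This Study they write that "forensic patients generally have low levels of treatment compliance", and they give this as a reason for leaving a sham arm out of the randomised part.

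**The concern.** Randomisation protects the comparison only if the patients analysed are those who were randomised, or if losses after allocation do not depend on the arm. In the order described, a patient can leave after his arm has been fixed and before any study measurement, and he then drops out of the data set as a nonresponse. Accepting 20 sessions of about 40 minutes asks more than accepting usual care plus two assessments, so the rate of refusal, or the kind of patient who refuses, may differ by arm.

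If it does, the consenting neurofeedback group could be more motivated than the consenting controls. Several outcomes could respond to motivation: BIS-11 and DAQ-SF are self-reported, and refusal of a drug test counts as a positive result (Participants). The control arm is open, so randomisation is the main safeguard here.

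Replacement restores the number but not the lost patients. The replacements are known to be willing before they are allocated, whereas the first 50 are not. The text also does not say how 25 per arm is kept if refusals are unequal between the arms.

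**Working it through.** **Order of steps.** In step 3 the words of time refer to the consent request, which the section places after the draw and assignment. No other section reverses this order, says that the arm is concealed at consent, or keeps decliners in the analysis.

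**The plan's own figure.** Inputs from Participants: "based on a 1-tailed alpha value of .05, a power value of 0.80", effect size 0.80, 21 per arm, raised to 25. Read as a standardised mean difference in a one-sided two-sample t-test, 0.80 gives 21 per arm (power 0.817), so the figure reproduces. At 25 per arm the power is 0.874. Moving consent does not affect these numbers.

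**Selection at entry (assumed model).** The document gives no refusal rates, so these are assumptions. Let motivation be standard normal and let the least motivated fraction p of an arm refuse. The mean motivation of those who stay is m(p) = φ(z_p)/(1 − p).

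- p = 0.30: 0.3477/0.70 = 0.497
- p = 0.05: 0.1031/0.95 = 0.109
- Gap between arms: 0.497 − 0.109 = 0.388 SD
- At 40% versus 10%: 0.644 − 0.195 = 0.449 SD
- At 20% in both arms: 0.350 − 0.350 = 0

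**From the entry gap to the planned test.** Randomized Controlled Trial and Statistical Analysis plan time (T0, T1) by group, which compares change. Let motivation correlate r0 with the outcome at T0 and r1 at T1. With equal outcome SDs, the bias in mean change is (r1 − r0) × gap. At 30% versus 5%:

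- r0 = r1 (both 0.3 or both 0.5): 0 × 0.388 = 0
- r0 = 0.2, r1 = 0.3, or r0 = 0.4, r1 = 0.5: 0.1 × 0.388 = 0.04 SD of the outcome

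**If motivation is related to change itself.** Let r be the correlation of motivation with the change score, with everything in SDs of change. Bias = r × gap. With 25 per arm the standard error is √(2/25) = 0.283, and the one-sided type I error is 1 − Φ(1.645 − bias/0.283). At 30% versus 5%:

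| r with change (assumed) | Bias (SD of change) | One-sided type I error |
|---|---|---|
| 0 | 0 | 0.05 |
| 0.2 | 0.08 | 0.085 |
| 0.3 | 0.12 | 0.109 |
| 0.5 | 0.19 | 0.169 |

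These rows show how the result depends on r. They are not estimates for this trial, because the document says nothing about r.

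**The case against.** **The arm may be unknown at consent.** The section does not say that it is disclosed. The remarks under This Study and in the Discussion, that a possible sham condition would deter patients, picture people deciding without knowing their arm. This stands as a limit: if the arm is hidden and cannot be guessed, refusal cannot depend on it. But those remarks concern a sham arm that was not adopted, and no sentence states concealment.

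**Replacements are randomised.** A reader might infer that topping up the depleted arm makes that part of the allocation non-random. The text does not support this, since it says that replacements receive randomised allocation. What stays open is how that is squared with 25 per arm.

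**The planned test compares change.** A reader might carry the entry gap straight through to a spurious benefit, for example 0.388 × 0.3 to 0.5 = 0.12 to 0.19 SD, and set it against the planned 0.80. With correlations taken with the outcome level, that describes an unadjusted comparison at T1, not the time-by-group test, in which a pure level difference cancels.

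**The model is extreme and its direction assumed.** It has the least motivated refuse with certainty. If acceptance tracked motivation with a correlation of only 0.5, the gap would halve to 0.19 SD. Controls might even refuse more often, since they are offered nothing added. Both points stand.

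**Some baseline information exists.** It would be too strong to say that nothing is known about decliners. The IFTE is scored twice a year from arrival and covers cooperation with treatment, drug tests are routine, and covariates come from case files. Using decliners' records may need permission, and BIS-11, DAQ-SF, the go/no-go task and the study EEG would still be missing for them.

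**Conclusion.** The point holds in conditional form. As written, allocation precedes written consent, and decliners are removed and replaced. With open arms of very unequal burden and no stated concealment at consent, this permits exclusions after randomisation that depend on the arm.

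Harm requires two things that the document neither states nor rules out: that the arm is known or guessable at consent, and that refusal differs by arm in rate or in type of patient. The text therefore does not show that the randomised comparison is broken; it shows that the stated procedure leaves it unprotected.

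The size cannot be derived. The entry gap of about 0.39 SD in motivation rests on assumed refusal of 30% versus 5% and on strict selection of the least motivated. The resulting bias in the planned test runs from zero, if motivation affects level only, upwards according to how far motivation is related to change. The correction is worth making before recruitment because it costs little, and patients lost in this way cannot be fully recovered later.

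**What to change.** Rewrite the Recruitment section in this order:

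1. Establish eligibility.
2. Obtain written consent to take part in either arm.
3. Complete T0.
4. Allocate at random, with the next assignment concealed.

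Count those who decline or withdraw before step 4 as nonresponse, and replace only them. Replace no one after allocation. Analyse all randomised participants in the arm to which they were assigned.

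Refusal then happens before any arm exists and cannot depend on it. The question of how to keep 25 per arm after unequal refusals also disappears, because only consenting patients are allocated.

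Cost: a few sentences and a change in the order of existing steps. A few T0 assessments may be spent on patients who withdraw before allocation. The target of 25 per arm and its power are unchanged. If the wording is merely loose and consent already comes first, the same rewrite settles the matter at no operational cost.
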